A clinical report of imaging examinations is essential to guide diagnostic and treatment decisions. Time to a clinical report can be a serious factor in diagnostic delays [16–18] with recognition that small delays for lung cancer diagnosis may contribute to higher stage at diagnosis [19] and also a deterioration in performance status that may influence suitability for treatment. In the setting of the lung cancer pathway, delays are often multifactorial, but may be contributed to by the time taken to report a chest X-ray (CXR). This is because the very first step in the lung cancer pathway is often the identification and reporting of a lung mass on a CXR, which should then trigger a staging computed tomogram (CT). The use of appropriately trained radiographers to undertake clinical reporting is not new. Skeletal radiograph reporting, for example, has become widespread across the UK [12, 20], and in many departments provides a significant contribution to reporting capacity [21, 22]. More recently, reporting radiographers have been trained to report CXRs [23, 24] and this has been proposed as a method of minimising CXR reporting times in patients with suspected lung cancer [25]. There is some limited evidence to date that has evaluated CXR accuracy rates of trained reporting radiographers in comparison with radiologists. Reporting radiographers (*n* = 40) were found to have high sensitivity (95.4%; 95% CI 94.4–96.3%) and specificity (95.9%; 95% CI 94.9–96.7%) at an objective, structured examination of 100 CXRs at the completion of an accredited training programme [23].

Recent work found poor compliance with suggested optimal diagnostic investigations for lung cancer, with 23% of patients in England receiving investigation and results within the recommended timeframes with significant variation between regions [26]. This study aims to evaluate the impact of radiographer reporting on the timeliness, accuracy and quality of CXR reports, as well as the impact on the overall lung cancer pathway in comparison with radiologists. These parameters have not previously been studied in lung cancer patients. The current study could act as a pilot study for a larger, multisite evaluation if results are positive.

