### Outcome measures

The primary outcome is to test the impact of radiographer immediate reporting of GP CXRs, with immediate CT where appropriate, on time from performance of the CXR to treatment (with intermediate time points)/discharge for lung cancer.

Secondary outcome measures include:Measurement of the effect on the speed of the lung cancer pathway:
(i)6-and 12-month survival (lung cancer and all-cause)(ii)Number of emergency admissions for lung cancer(iii)Performance status at time of decision to treat(iv)Stage at diagnosis of lung cancer
Measurement of the effect of the pathway on efficiency including:
(i)The impact of immediate GP CXR reporting on the number of urgent respiratory cancer (2WW) referrals(ii)The accuracy and usefulness of radiographer CXR reporting in clinical practice(iii)The cost-effectiveness of radiographer reporting(iv)The influence of immediate GP CXR reporting, with immediate CT where appropriate, on the number of first 2WW appointments with all radiology results available
Measurement of the number of repeat CXRs performed in a timely fashion for suspected infectionThe effect of immediate reporting of GP CXRs on patient satisfaction

In addition to comparison as per randomisation within Homerton University Hospital, primary outcomes will be compared with a neighbouring hospital, Newham University Hospital.

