### Index diagnosis by thoracic radiologist

Chest X-rays that are found to have discordant reporting radiographer and consultant radiologist reports at peer review will have an index diagnosis. For cases that have undergone a subsequent CT scan of the chest and abdomen, the CT report will constitute the index diagnosis. CXR reports, either reporting radiographer or consultant radiologist, will be deemed a true positive if CT confirms the CXR diagnosis and a false positive if the CT is normal or another pathology is demonstrated. True positive and true negative will be a consensus decision and corroboration between the CT and clinical history between a respiratory physician and a thoracic radiologist. Assessment of report accuracy will be made blinded to the origin (reporting radiographer/consultant radiologist) of the CXR report.

For cases that have not had a CT performed, an independent expert thoracic consultant radiologist will constitute the index diagnosis. The index radiologist will feed back the diagnosis via a standardised proforma. All available thoracic imaging (X-ray, CT) for the patient will be sent via the Image Exchange Portal (IEP) to the Royal Brompton Hospital. IEP is an established, secure method of transferring radiology cases for external review within the NHS. A thoracic consultant radiologist will review the available imaging and provide the definite diagnosis. CXR reports, both reporting radiographer and consultant radiologist, will be deemed a true positive if the thoracic radiologist confirms the CXR diagnosis and a false positive if the thoracic radiologist interpretation is normal or another pathology is demonstrated.

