### Statistical considerations

#### Sample size

For the primary endpoint in this pilot study, time to treatment decision for lung cancers, if we expect an 11-day advance in time to first treatment decision, with a standard deviation of 14 (previous audit data suggest this degree of variation), 26 cancers in each group will confer 80% power (two-sided testing, 5% significance level), for the internal randomised comparison. We expect around 50 cancers per year in Homerton University Hospital (HUH), so we will have adequate power for this difference. A reduction in time to diagnosis of 2 weeks was found to improve mortality of lung cancer patients so this difference could be clinically significant in the current pilot study [34]. If we anticipate a 12-day, instead of an 11-day advance in diagnosis, we would only need 22 in each arm, 44 cancers in all, for 80% power. For the external comparison, assuming that Newham University Hospital has a similar number of lung cancers per year, therefore, we would have close to 90% power for the same difference and standard deviation. If we also compare times to diagnosis for all persons referred to the pathway (lung cancer and non-lung cancer diagnoses), previous data suggest an average of 18 days and a standard deviation of 14. If the intervention improves this by 7 days on average, with a standard deviation of 15, we would need 73 subjects in each group referred to the pathway to achieve 80% power (two-sided testing, 5% significance level). Thus, both the internal and external comparisons will be adequately powered.

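### The accuracy rules name no target condition and no false negative, so a lung cancer reported as infection is scored as a false positive rather than as a missed cancer

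*Protocol article*

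**What the plan says.** One of the secondary outcomes under Outcome measures is "The accuracy and usefulness of radiographer CXR reporting in clinical practice". The rules for judging accuracy are in the section Index diagnosis by thoracic radiologist.

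- **Who gets an index diagnosis.** "Chest X-rays that are found to have discordant reporting radiographer and consultant radiologist reports at peer review will have an index diagnosis". No index diagnosis is described there for films on which the two readers agree.
- **When a CT was done.** The CT report is the index. A report from either reader "will be deemed a true positive if CT confirms the CXR diagnosis" and is "a false positive if the CT is normal or another pathology is demonstrated".
- **When no CT was done.** An independent thoracic radiologist is the index. The wording is parallel: a report is "a false positive if the thoracic radiologist interpretation is normal or another pathology is demonstrated".
- **Other categories.** The CT paragraph adds that "True positive and true negative will be a consensus decision", reached by a respiratory physician and a thoracic radiologist from the CT and the clinical history. It gives no criterion for a true negative. The no-CT paragraph does not mention true negatives. The term false negative appears nowhere in the article.

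**The concern.** True and false positive only have a meaning relative to a stated condition. Here the reference is whatever diagnosis the report happened to name, and it changes from film to film. The false-positive rule is wide enough to take in a report that named the wrong disease while a cancer was present. For a lung cancer pathway that report is a missed cancer.

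A missed cancer is arguably the error that matters most when radiographer and radiologist reports are compared, and accuracy is part of the aim stated in the Background. The Health economic assessment section also lists diagnostic accuracy for cancer and for non-cancer among its inputs. A cancer-specific figure cannot be taken from categories that are not tied to cancer.

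**Working it through.** The article states no accuracy figure, target or sample size, so there is nothing to reproduce. The check applies the stated rule to each combination of report and index diagnosis and sets the result beside a classification with lung cancer as the target. The labels true and false positive are read in their ordinary sense, as applying to reports that name an abnormality.

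| Report | Index diagnosis | Rule as written | Target = lung cancer |
|---|---|---|---|
| Cancer | Cancer | True positive | True positive |
| Infection | Cancer | **False positive** (another pathology) | **False negative** |
| Normal | Cancer | **No stated cell** | **False negative** |
| Cancer | Infection | False positive | False positive |
| Cancer | Normal | False positive | False positive |
| Infection | Infection | True positive | True negative |
| Infection | Normal | False positive | True negative |
| Normal | Infection | No stated cell | True negative |
| Normal | Normal | True negative by consensus, no criterion (CT paragraph only) | True negative |

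No row yields a false negative under the rule as written. The rows in bold are the missed cancers.

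To see the effect on a summary measure, take one reader and the discordant films whose index is lung cancer. Let *a* be the reports suspicious for cancer, *b* those naming another disease, and *c* those calling the film normal.

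- With lung cancer as the target, the true positives are *a* and the false negatives are *b* + *c*. The proportion detected on these films is *a* / (*a* + *b* + *c*).
- Under the rule as written, *a* are true positives, *b* join the false positives, *c* are unassigned, and the false-negative count is empty. A calculation of TP / (TP + FN) therefore loses *b* + *c* from its denominator.
- The *b* reports reappear in the false-positive count. They lower TP / (TP + FP) and TN / (TN + FP) for a reason that has nothing to do with over-calling cancer.

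The direction is fixed by the text. The size depends on *b* and *c*, and the article gives no value for either.

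**The case against.** **The article does not say it will calculate sensitivity.** This is correct. The outcome is accuracy and usefulness, and Data analysis gives no accuracy formula. The consequence for sensitivity is conditional on its being used. The misfiling is not conditional, because the rule assigns the category.

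**A normal report makes no positive call, so a false negative is simply the unstated complement of a true negative.** This stands for normal reports, which are better described as having no stated cell than as wrongly filed. It does not help the report of infection. That report names an abnormality, the index shows a different one, and the false-positive wording claims it.

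**Scoring the named diagnosis is a legitimate approach, and the report of infection was a false positive for infection.** This is also fair, since accuracy here is not confined to cancer. But a diagnosis-level scheme would also need an entry for the cancer that was missed, and none is provided.

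**Full definitions may sit in the complete protocol or the proformas.** They may, and an absent definition alone would not be a finding in a condensed article. Here the article states a rule, twice, and the rule as stated misclassifies.

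**A stronger reading is tempting.** A reader might combine the "high sensitivity (95.4%; 95% CI 94.4–96.3%) and specificity (95.9%; 95% CI 94.9–96.7" percent from the Background with "We expect around 50 cancers per year in Homerton University Hospital" to count the cancers that would be hidden, and conclude that sensitivity will be overstated by a known amount. The documents do not support this. The earlier figures come from an objective structured examination of 100 films and are not said to be for cancer. The expected cancers are not all said to present through a general practice X-ray. The rule reaches discordant pairs only, and their number is not given.

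**Conclusion.** The point holds in a limited form. As written, a report naming another disease when the index shows lung cancer is scored as a false positive, and a normal report in the same situation has no category. A cancer-specific accuracy measure taken from these cells would omit missed cancers. The conclusion rests on the stated wording and on the ordinary meaning of the labels; it needs no numerical assumption, and no size can be attached to it.

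Its reach is also limited. It concerns one item of a secondary outcome. The rule is applied to both readers, blinded to source, and does not enter the time-to-treatment comparison. The article does not say that these cells supply the economic model, so an effect there is possible but not established. Nor should a reader infer that correcting the cells would yield overall sensitivity. Where both readers miss a cancer and their reports agree, no index diagnosis is triggered and the cancer stays unverified; films on which both correctly suspect cancer are not indexed under this section either.

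**What to change.** In both paragraphs of Index diagnosis by thoracic radiologist, replace the confirm-or-not rule with a two-by-two table for each reader, with lung cancer as the named target: report suspicious for lung cancer (yes or no) against index diagnosis of lung cancer (yes or no). Define all four cells:

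- **True positive:** suspicious report, index lung cancer.
- **False negative:** report not suspicious for cancer, index lung cancer, whatever else the report named.
- **False positive:** suspicious report, index anything other than lung cancer.
- **True negative:** report not suspicious, index not lung cancer.

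If accuracy for infection or other diagnoses is wanted, use a separate table for each.

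Add one sentence stating that the table covers only discordant pairs that receive an index diagnosis. It supports a comparison of the two readers on those films and does not by itself estimate overall sensitivity.

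The cost is protocol wording and one field on the existing proforma. Patient care does not change.

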## Components of the chest X-ray reporting pathway

### Reporting radiographer chest X-ray report

All reporting radiographers participating in the study have completed an accredited postgraduate certificate in adult CXR reporting (experience 1–8 years) and currently provide CXR reports in clinical practice. All CXRs referred by GP on eligible patients (aged over 16 years, no active history of lung cancer) will receive a reporting radiographer report. In line with current practice, a narrated report will be provided rather than a structured report. Image interpretation will occur on Picture Archiving and Communication System (PACS) workstations and the report entered into PACS and transferred to the patient electronic record. If the reporting radiographer requires additional investigations (repeat X-ray due to inadequate initial X-ray, additional X-ray view, CT of the chest and abdomen), these will be arranged by the reporting radiographer at time of the CXR report.

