### Consultant radiologist chest X-ray report

All CXRs will receive a consultant radiologist report (general radiologists; experience range 2–21 years post FRCR), blinded to the reporting radiographer CXR report. Consultant radiologist reporting will occur at the next session following the reporting radiographer report. Interpretation will occur using PACS workstations and the report will be entered into a secure database.

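### On discordant films, the radiographers' and the consultants' positive calls are likely to be verified by different mixes of CT and expert re-read, which can bias the accuracy comparison in either direction

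*Protocol article*

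**What the plan says.** All references are to the protocol article.

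- **Which films get a reference** (Index diagnosis by thoracic radiologist): only disputed films do, since "Chest X-rays that are found to have discordant reporting radiographer and consultant radiologist reports at peer review will have an index diagnosis". Concordant films get none.
- **CT branch** (same section): "For cases that have undergone a subsequent CT scan of the chest and abdomen, the CT report will constitute the index diagnosis". Corroboration with clinical history and a consensus between a respiratory physician and a thoracic radiologist are described here.
- **No-CT branch** (same section): "For cases that have not had a CT performed, an independent expert thoracic consultant radiologist will constitute the index diagnosis". Further on: "A thoracic consultant radiologist will review the available imaging and provide the definite diagnosis". Clinical history and later diagnosis are not mentioned in this branch.
- **Scoring**: in the CT branch, "CXR reports, either reporting radiographer or consultant radiologist, will be deemed a true positive if CT confirms the CXR diagnosis"; in the no-CT branch, "CXR reports, both reporting radiographer and consultant radiologist, will be deemed a true positive if the thoracic radiologist confirms the CXR diagnosis". Accuracy is assessed blind to which profession wrote the report.
- **Radiographer's report** (Reporting radiographer chest X-ray report): it goes into PACS and on to the patient's record. If further imaging is needed, CT included, "these will be arranged by the reporting radiographer at time of the CXR report".
- **Consultant's report** (Consultant radiologist chest X-ray report): it is made at the next session, blind to the radiographer's report. "Interpretation will occur using PACS workstations and the report will be entered into a secure database".
- **Who arranges CT** (CT of the chest): either type of reporting practitioner.
- **Use of the result** (Outcome measures): accuracy and usefulness of radiographer reporting is one of the efficiency items among the secondary outcomes. Diagnostic accuracy is also listed among the inputs to the Health economic assessment.

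**The concern.** The two references differ in quality. CT adds information that the chest X-ray does not hold. An expert's review of existing imaging, where that is essentially the disputed film, measures agreement with a third reader. It cannot reveal a cancer that the expert also fails to see, and it can endorse a suspicion that CT would have dismissed.

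That would do little harm to a comparison of readers if the choice of reference were unrelated to which reader was positive. Here it probably is related. A film that only the radiographer calls suspicious has a direct route to CT; a film that only the consultant calls suspicious has no stated one. This is differential verification. Blinding the assessor does not remove it, because the imbalance arises before any assessment. It falls on the discordant films, which are the ones that separate the two readers.

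**Working it through.** The document gives no figure for discordance, CT uptake or accuracy of the re-read, so there is no stated figure to reproduce. The check has two parts.

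**1. The route to each reference, read across the sections**

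| Discordant film | Stated route to CT | Likely reference |
|---|---|---|
| Suspicious to radiographer only | Report enters the record; radiographer arranges CT when reporting | Mostly CT |
| Suspicious to consultant only | Report enters a study database; either practitioner may arrange CT; no section says that such a film goes to CT | Uncertain, with more re-reads |

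The second column is stated. The third is an inference from it.

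**2. What unequal CT uptake does to two equally accurate readers (illustration)**

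All inputs are assumptions. Among films that only one reader calls positive, let

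- *p* = true share positive, the same for both readers;
- *c* = share that gets CT (*c*R for radiographer-only, *c*C for consultant-only films), with CT taken as error-free;
- Se, Sp = sensitivity and specificity of the expert re-read.

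Share confirmed by the re-read: *r* = *p*·Se + (1 − *p*)(1 − Sp).

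Share confirmed overall: *c*·*p* + (1 − *c*)·*r*.

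Spurious difference, radiographer minus consultant: (*c*R − *c*C)(*p* − *r*), where *p* − *r* = *p*(1 − Se) − (1 − *p*)(1 − Sp).

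The values tried were *p* = 0.1, 0.3 and 0.5, with Se/Sp = 0.60/0.95, 0.80/0.90 and 0.90/0.80. The two extremes are:

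- *p* = 0.1, Se/Sp = 0.90/0.80: *r* = 0.09 + 0.18 = 0.27, so *p* − *r* = −0.17.
- *p* = 0.5, Se/Sp = 0.60/0.95: *r* = 0.30 + 0.025 = 0.325, so *p* − *r* = +0.175.

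| CT uptake, radiographer-only v consultant-only | Lowest difference | Highest difference |
|---|---|---|
| 100% v 0% | −17.0 points | +17.5 points |
| 90% v 10% | 0.8 × (−0.17) = −13.6 | 0.8 × 0.175 = +14.0 |
| 90% v 50% | 0.4 × (−0.17) = −6.8 | 0.4 × 0.175 = +7.0 |
| 90% v 90% | 0 | 0 |

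Two things follow. The bias scales with the difference in CT uptake and vanishes when uptake is equal. Its sign depends on whether the re-read misses more true positives or endorses more false ones, and the document does not settle that.

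**The case against.** The case for leaving the plan alone has several parts.

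- **Same reference within a film.** A reader might infer that the two readers are scored against different references. The text does not support that: in both branches both reports on a film face one index diagnosis. What can differ is the mix of references behind each reader's positive calls. The stronger reading falls; the narrower one stands.
- **Either practitioner may arrange CT.** CT of the chest says so. Control and Off-protocol radiographer reporting also allow a consultant to give the urgent report, and reports are compared within three working days. If consultant-only suspicions regularly lead to CT, the asymmetry shrinks or disappears. This stands as a limit. But naming the study database as the destination of the consultant's report, with no statement of what a consultant-only suspicion triggers, leaves the inference reasonable.
- **Later cancers may be captured anyway.** A reader might infer that the no-CT rule ignores every lung cancer diagnosed later. That goes too far. The CT branch covers a subsequent CT with no time limit and whoever ordered it, and the expert is sent whatever chest imaging exists, not only earlier images. Many later-diagnosed cancers would be caught this way. What remains is a cancer without such a CT, or one whose CT came after the index diagnosis was settled; the document gives no cut-off.
- **No claim in one direction.** A reader might infer a sensitivity gap favouring the radiographer. For example, suppose each reader detects 45 cancers, 5 of them alone; radiographer-only cancers go to CT and consultant-only cancers to the re-read. If the re-read confirms a share *q* of the latter, the gap is 5(1 − *q*)/(45 + 5*q*): 5.3 points at *q* = 0.5 and 1.0 point at *q* = 0.9. The arithmetic is right, but the inputs are invented, and 40 of those cancers are concordant films, which get no index diagnosis. Specificity can be biased in the opposite direction.
- **Expert review is a usual choice** where CT was not clinically indicated and the study adds no tests. That is fair. It justifies having the branch, but not treating its result as equivalent to CT.

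**Conclusion.** The point holds in a limited form. The protocol fixes two references of unequal quality for discordant films, and its account of where each report goes makes CT verification likely to depend largely on the radiographer's own call. The secondary accuracy comparison can therefore be biased in either direction, and a biased estimate would carry into the economic model that uses it.

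The size cannot be derived from the document. The range of −17 to +17.5 points is an illustration for wholly one-sided CT uptake, error-free CT and assumed re-read accuracy; equal uptake gives 0. The conclusion rests on the inference that consultant-only suspicious films reach CT less often, which no section states. The primary outcome, time from chest X-ray to treatment or discharge, is not touched. This should be corrected, but it does not threaten the trial's main comparison.

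**What to change.** 1. **No-CT branch of the index diagnosis.** Apply the same corroboration with clinical history as in the CT branch. For the call that a film is suspicious for lung cancer, count a lung cancer diagnosed by the end of follow-up as reference-positive, whatever the re-read says.
2. **Reporting.** Show discordant-film results separately by reference type (CT or expert re-read) and by direction (radiographer-only or consultant-only positive). Describe results that rest on the re-read alone as agreement with an expert, not as accuracy.
3. **Consistency.** Reconcile the sections on the radiographer's report, the consultant's report and CT of the chest on what follows a report that only the consultant finds suspicious. Which rule applies is a clinical matter for the investigators.

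**Cost.** Items 2 and 3 are mainly wording and tabulation. Item 1 delays final cancer scoring until follow-up closes and needs discordant films to be linked to lung cancer diagnoses. The unique identifier assigned at the chest X-ray should help, but the document does not show that cancer follow-up is collected for every discordant film. Some bias may remain: if consultant-only positive patients are investigated less, some of their cancers may stay undiagnosed. For that reason diagnosis by the end of follow-up is added to the rule here and does not replace the other references. The split by direction makes any remaining imbalance visible.
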